### Current research results from the home-visiting program Pro Kind

Data collection at the time points at 6, 12 and 24 months after birth of the reference child showed small positive effects of the Pro Kind program on maternal feelings of parental self-efficacy (*β* = .03; Wald = 4.05; *df* = 1; *p* = .044), social support (*β* = .04; Wald = 3.85; *df* = 1; *p* = .050) and their knowledge about child-rearing (*β* = .03; Wald = 3.43; *df* = 1; *p* = .064) [43]. In addition, fewer women in the treatment group stated that they suffered from depressive mood 24 months after birth (OR 0.54, *p* = .070]. This finding was confirmed by administrative health insurance data that showed that fewer mothers in the treatment group used antidepressants (*p* = .040^1^). The increased maternal wellbeing may be one reason why in the treatment group fewer pregnancy terminations (conditional on a further pregnancy) than in the control group were observed (OR 0.54, *p* = .090). This might also as a consequence have led to a higher rate of second births 36 months after birth (OR, 1.48, *p* = .030). Regarding the children, the intervention resulted in an improvement in the cognitive development of the girls in the treatment group (at 6 months, ES 0.29, *p* < 0.05; at 12 months, ES 0.28, *p* < .05; at 24 months, ES 0.24, *p* < .01), whereas no improvement could be found in the boys’ cognitive skills. One possible explanation for the gender-specific effect could be that the intended treatment, consisting of the parents reading to, and singing with, their children, was implemented more often with female children compared to male children [45–47].

In addition, the model project Pro Kind is being evaluated by encompassing economic research, for which the most important goal was, and is, to conduct a cost-benefit analysis. The costs for providing the home-visiting program were thereby contrasted with the monetized benefits of the intervention, whereby, in conclusion, the program’s return on investment (ROI) can be determined. The cost of an average intervention was approximately €8.700 [48]. Since the home-visiting program Pro Kind seeks to achieve improvements in several different domains, the saving effects should be different in the various domains and concern different fiscal areas.

## Methods/design

The Follow-Up Study Regarding the Medium-Term Effectiveness of the Home-Visiting Program “Pro Kind,” Based on a Randomized, Controlled Research Design (official study title: “Follow-Up Untersuchung zur mittelfristigen Wirksamkeit des Hausbesuchsprogramms Pro Kind anhand eines randomisierten kontrollierten Forschungsdesigns, Acronym: Pro Kind Follow-up”) is funded by the German Federal Ministry of Education and Research (BMBF funding codes: 01EL1408A, 01EL1408B, 01EL1408C), So far, it has been possible to reestablish contact with a number of families (as of today, approximately 500 families could be reached, re-recruitment is still ongoing, first family contacted on 15 June 2015) and request participation in a follow-up survey. When the (reference) children are at primary school age (7–9 years), the medium-term effects of the home-visiting program Pro Kind is to be studied with the help of multimethod survey approaches from the perspective of the children as well as the mothers, in addition to administrative data. The study is registered in the German Clinical Trial Register (trial ID: DRKS00007554, date of registration: 11 June 2015). The main sponsor of the Pro Kind Follow-up is the Criminological Research Institute of Lower Saxony (KFN, principal investigator [name]). Secondary sponsorship is provided by the University of Rostock ([name]. [name]) the Institute for Employment Research Nuremberg (IAB, [name]) as well as the University Clinic Leipzig ([name] [name]).

### Procedure

The follow-up study can be subdivided in to six domains (1) interviewer training, (2) assessment of contact details, (3) telephone interviews, (4) on-site interviews and developmental tests, (5) acquisition of administrative data and (6) data analysis. The sponsoring institutions will be involved in these domains as follows: KFN: (1), (2), (3), (4), (5); IAB: (1), (2), (5), (6); University of Leipzig: (1), (4), (6), University of Rostock: (1). An overview of the ProKind Follow-up schedule can be found in Fig. 1. The protocol is reported according to the Standard Protocol Items: Recommendations for Interventional Trials (SPIRIT; Fig. 1 and Additional file 1).

**Fig. 1 Fig1:**
[figure not shown]
Schedule of Pro Kind Follow-up

#### Interviewer training

All interviewers underwent several days of intensive training as preparation for the home interviews. They received general information regarding child development and background knowledge on the demographic characteristics of the participants. Special focuses of the training were interview and communication techniques including de-escalation methods. Interviewers were sensitized for signs of suicidality and child abuse and instructed how to handle these. They were prepared for problematic situations such as disruptive behavior of the child. The interviewers were certified for the correct application of the measures and tests. Certification was, whenever necessary, provided by external institutions (i.e., for the Kinder-DIPS). All project staff members, including research assistants and interns, were sworn to confidentiality (according to §5 BDSG) upon start of their employment. Should signs for child abuse be uncovered during the study, a conflict between psychological /scientific confidentiality and the obligation to protect the child’s wellbeing might arise. In such a situation, the specific case and the suspicions of the interviewer will be first discussed with the project leader and the necessity to involve third parties evaluated. Before legal action is pursued it will be examined whether personal communication and sensitizing parents regarding the issue at hand as well as encouraging help-seeking behavior in the affected families are sufficient and justifiable (§4 Absatz 1 KKG). It is, furthermore, possible to request anonymous legal advice from local authorities (§4 Absatz 2 KKG). Based on German law, personal information will only be relayed to third parties when the child’s wellbeing is clearly at stake and any attempts of arranging for help remained unsuccessful (§4 Absatz 3 KKG). All members of staff are extensively trained regarding legal matters as well as personal behavior in such situations.

#### Assessment of contact details

Participants are first contacted by the KFN via mail. In this letter participants are informed about the study and can send back a postcard with a current telephone number. In case this initial mail cannot be delivered, the local registration office (Einwohnermeldeamt) is contacted and asked for the current contact details (name and address) of participants. A project assistant then establishes first personal contact via telephone. During this initial phone call appointments for the home visits as well as for the telephone interviews are scheduled.

#### Computer-aided telephone interviews (CATI)

As during the first program phase, scales from the German Socio-Economic Panel (SOEP) [49] as well as the study regarding the health of children and youths in Germany (KiGGS [50]) are used to gather socio-demographic data as well as data regarding the use of health services. In addition, psychometric scales are presented to assess relevant areas that include the mothers’ current living conditions (e.g., the mothers’ general health and social support), as well as that of the children (e.g., general development and socio-emotional development). Furthermore, parts of a fully standardized diagnostic interview, corresponding to the Expert System for Diagnosis of Mental Disorders (Diagnostisches Expertensystem für Psychische Störungen, DIA-X; [51]), are conducted to identify possible mental disorders and problems on the part of the mothers. A trained project team member conducts two telephone interviews with each participant.

#### On-site interviews

In a 2.5-h home visit, two professionally trained project team members conduct structured interviews with the mother and developmental tests with the reference child. These outcome assessors are unaware whether the families are part of the intervention or control group. After an introductory and instruction phase on the part of a project team member, the mother’s consent for testing the children is obtained. All relevant materials are presented to her and she is, furthermore, informed in detail about the test procedures. Subsequently, the *Diagnostic Interview for Mental Disorders for Children and Adolescents* (Kinder-DIPS; [52]) is conducted, whereupon the mother is given a paper-pencil questionnaire to complete. In case an interview or psychological testing is too exhausting for mother or child it is possible to schedule additional appointments to continue the interview and/or testing.

At the same time – with the mother’s consent – the second project team member carries out a structured interview with the child. The children are thereby interviewed regarding their experiences of neglect, based on picture card-based, age-appropriate, structured interviews (Multidimensional Neglectful Behavior Scale, MNBS [53]) and regarding minor physical abuse (Conflict Tactic Scale, CTS-CV [54]). In order to prevent severe stress for the children, only a few, low-intrusive scales are used. No questions are asked concerning experiences of severe violence. The children, furthermore, complete the test battery BUEGA (*Basisdiagnostik Umschriebener Entwicklungsstörungen im Grundschulalter* (Basic diagnostics of specific developmental disorders in elementary school children [55]) and three structured game situations regarding (1) risk behavior according to Dohmen and colleagues [56], (2) pro-social behavior according to Fehr and colleagues [57] and (3) time preference according to Mischel and colleagues [58]. The testing and games that are carried out with the children are entirely age appropriate and playful. Nevertheless, the mere length of the session requires a significant amount of focus and motivation on behalf of the child. It is, hence, possible to divide the tests between at least two sessions should the child show signs of exhaustion or lack of motivation. The test administrator will, together with the mother, make sure that the child’s needs are met and a good relationship of child and test administrator can be established to ensure optimal testing conditions. The children’s participation is entirely voluntary. Children are informed that there will be no negative consequences should they decide not to participate. Furthermore, children are assured that the answers that they provide are confidential. Children are also informed of their right to quit the interview or testing at any moment.

#### Expert judgment

After the on-site interviews, both project team members individually gather observations on site in the domestic environment regarding the living situation, the wellbeing of the child, as well as the quality of the parent-child relationship. Observations are rated according to the scales of the Home Observation for Measurement of the Environment (HOME [59]).

#### Compensation of participants

All participants receive €80 as compensation for the time invested in the telephone interview, face-to face interview and developmental testing. In case only one interview can be conducted the participant receives €30 (telephone interview) or €50 (home visit), respectively. Every child receives a little gift after the home visit (worth approx. €10).

#### Communication of disconcerting test results

The results of the developmental tests (intelligence test, vocabulary test) and diagnostic interviews (DIA-X, Kinder-DIPS) are shared with the parents and explained using an appropriate, yet easily understandable, language. The project staff is available should participants have further questions regarding test results. Upon request project staff members will also assist in the arrangement of counseling or support services for mother or child.

#### Administrative data

In addition to the survey methods mentioned above, administrative data from various sources are used. According to the first project phase, data regarding inpatient and outpatient treatment, as well as medication, aids, mother-child therapies and speech therapy are made available by AOK Niedersachsen, Bremen and Sachsen (German public health insurance company). Here, among other information, it is documented whether vaccinations, early screenings, etc. have been attended at health facilities. Furthermore, information is gathered regarding previous employment, phases of unemployment, and participation in measures during unemployment as well as employment details from the Technical Data Center (FDZ) of the Institute for Employment Research (IAB) of the Federal Employment Agency in Nuremberg. It was possible for the participants to provide self-report data but not grant the researchers access to administrative data.

#### Data handling and monitoring

Data collection and management is overseen by the KFN data manager. He is employed directly by the KFN and not involved in the project either monetarily or scientifically. All project team members have received extensive professional training regarding the application of the measures, data confidentiality but also regarding possible signs of suicidality, child abuse or neglect. All telephone interviews are recorded and evaluated by a second research assistant regarding proper conduct as well as signs of suicidality, child abuse or neglect. Audio- and video-recordings are saved with the primary sponsor and only shared with secondary sponsors for data analysis as stated in the consent form (see Additional file 2). Neither audio nor video transcripts contain personal information beyond the child’s first name and the mother’s initials. After data analysis, video material has to be blurred for alienation purposes or deleted. All outcome assessors were blinded regarding intervention vs. control group membership of the families. Questionnaires were transported in a sealed envelope without identifying personal information beyond a code for longitudinal matching. Personal information was only used for contacting the participants. The personal information is not stored together with the outcome data and is only accessible on a need to know basis.

### Evaluation of effectiveness

The main focus of the scientific work objective is to answer the following research questions (please see Fig. 2 for the intervention’s internal logic. The model shows its hypothesized, causal mechanisms based on a model presented by Olds [10]):

**Fig. 2 Fig2:**
[figure not shown]
Intervention’s logic model following Olds [10]

*Research question 1*: *Does the home-visiting program Pro Kind exert a positive effect on the cognitive and socio-emotional development, as well as on the physical health of the child in the medium term?**Hypothesis 1.1*: The home-visiting program has a positive effect on the child’s cognitive development and school performance.*Hypothesis 1.2*: The home visits have a positive effect on the child’s mental health.*Hypothesis 1.3*: The home visits have a positive effect on the child’s socio-emotional development.*Hypothesis 1.4*: The home visits have a positive effect on the child’s life satisfaction.*Hypothesis 1.5*: The home visits influence the child’s preferences (risk behavior, pro-sociality and time preference).

*Research question 2*: *Does the home-visiting program Pro Kind, in the medium term, influence the frequency and intensity of parental violence and child neglect?**Hypothesis 2.1*: The home visits result in improved parenting skills (less inappropriate parenting behavior).*Hypothesis 2.2*: The home visits reduce or prevent child abuse as well as the frequency of physical violence.*Hypothesis 2.3*: The home visits reduce or prevent child neglect.

Research question 3: *Does the home-visiting program Pro Kind have a positive effect on the psychosocial situation as well as on the mothers’ mental health?**Hypothesis 3.1*: The home visits have a positive effect on the mother’s perceived social support.*Hypothesis 3.2*: The home visits influence the mother’s mental health.*Hypothesis 3.3*: The home visits result in more stable partnerships with less frequent partner change, greater satisfaction with the partnership and less domestic violence in the partnership.*Hypothesis 3.4*: The home visits improve the parental self-efficacy expectations concerning the parenting tasks.*Hypothesis 3.5*: The home visits have a positive effect on the perceived stress resulting from the mother’s parenting tasks.*Hypothesis 3.6*: The home visits have a positive effect on the mother’s life satisfaction.

*Research question 4*: *Does the home-visiting program Pro Kind positively influence the socio-economic situation in the family?**Hypothesis 4.1*: The home visits increase the share of mothers in employment or education programs.*Hypothesis 4.2*: The home visits reduce the families’ use of welfare payments (*SGB II, SGB III* and *SGB VIII (social security codes)*).*Hypothesis 4.3*: The home visits have a positive effect on the family’s living situation.*Hypothesis 4.4*: The home visits influence the timing or frequency of a renewed pregnancy and births.

*Research question 5*: *Does the home-visiting program Pro Kind have a positive effect on the family’s physical health and health service utilization?**Hypothesis 5.1*: The home visits improve the mothers’ physical health.*Hypothesis 5.2*: The home visits increase the frequency of pediatric primary care use (e.g., screenings, vaccinations, child’s oral health care and dentist visits).*Hypothesis 5.3*: Home visits reduce the children’s hospital visits (outpatient or inpatient) caused by accidents and injuries.

Table 1 briefly describes the procedures used to evaluate the program. It is of special importance whether the underlying constructs are (1) based on a direct efficiency hypothesis of the Pro Kind program (primary outcome) or (2) based on an efficiency hypothesis, but one that must be regarded as less probable than a primary outcome (i.e., secondary outcome) for the following two reasons. First, the intervention did not directly focus on the secondary outcomes, (e.g., child preferences); second, we have less power for the outcomes, (e.g., administrative health services utilization data is only available for one third of the sample as we only cooperate with the largest health insurance company in Germany). Lastly, (3) a construct will be assessed for future research questions but is not regarded as an original aim of the intervention (i.e., no outcome). Due to the amount of data that is to be gathered, in the following only the primary and secondary outcome domains will be presented. The documentation of the study can furthermore be viewed at the German Register of Clinical Trials (DRKS; ID: DRKS000007554. Registration date 11 June 2015; updated on 24 August 2017). In the following, the procedures presented in Table 1 will be described in more detail.

**Table 1 Tab1:** List of procedures of biopsychosocial evaluation of the Pro Kind Follow-up

Hypothesis	Construct	Operationalization	Primary or secondary outcome domains	Informant	Data source
*Hypothesis 1.1*: The home-visiting program has a positive effect on the child’s cognitive development and school performance	Child’s school performance	Basic diagnostics of specific developmental disorders of speech and language at primary school age (BUEGA [55])	Primary outcome domain	Child	Testing by trained test administrator
	Child’s cognitive development				
	Child’s specific developmental disorders				
*Hypothesis 1.2*: The home visits have a positive effect on the child’s mental health	Child’s behavioral problems and emotional disorders	Child Behavior Checklist (CBCL 6/18 R [60]), German version: [61]	Primary outcome domain	Mother	Questionnaire
	Child’s attention deficit hyperactivity disorder and social behavior disorders (suspected diagnosis)	Module from the diagnostic interview of mental disorders in children and youths (Kinder-DIPS [52])		Mother	Interview by trained and certified staff
	Child’s anxiety disorders (suspected diagnosis)				
	Child’s affective disorders (suspected diagnosis)				
*Hypothesis 1.3*: The home visits have a positive effect on the child’s socio-emotional development	Child’s social skills	Social Skills Improvement System (SSIS [62]), German version: author’s translation	Secondary outcome domain	Mother	Questionnaire
	Child’s aggression	Questionnaire regarding children’s aggressive behavior (FAVK [63])		Mother	Questionnaire
	Child’s psychopathy	Inventory of Callous-Unemotional Traits (ICU) ([64]), German version by Essau		Mother	Questionnaire
*Hypothesis 1.4*: The home visits have a positive effect on the child’s life satisfaction.	Child’s general life satisfaction	Inventory to measure the life quality of children and youths (ILK [65])	Primary outcome domain	Child	Survey by trained test administrator
*Hypothesis 1.5*: The home visits influence the child’s preferences (risk behavior, pro-social behavior and time preference).	Child’s pro-social behavior	Game for interpersonal allocation decisions ([57]).	Secondary outcome domain	Child	Testing by trained test administrator
	Child’s risk behavior	Investment decisions in a lottery ([56])			
	Child’s time preference	Game for temporary allocation decisions ([58])			
*Hypothesis 2.1*: The home visits result in improved parenting skills (less inappropriate parenting behavior)	Mother’s dysfunctional parenting	Parenting Scale (PS) ([66]), German version: target-group-specific adaptation by the authors	Primary outcome domain	Mother	Questionnaire
	Mother’s non-violent disciplining	Conflict Tactic Scale Child Report (CTS-CR [68]), interview of the children with picture cards. German version: translation by the AMIS group / Conflict Tactic Scale Parent Child (CTS-PC [67]), German version: target-group-specific adaptation by the authors		Child / Mother	Interview through trained test administrator (Child) / Questionnaire (Mother)]
*Hypothesis 2.2*: The home visits reduce or prevent child abuse and the frequency of physical violence	Mother’s child abuse	Conflict Tactic Scale Parent Child (CTS-PC) ([54]), German version: target-group-specific adaptation by the authors	Primary outcome domain	Mother	Questionnaire
	Mother’s “Minor” aggression	Conflict Tactic Scale Child Report (CTS-CR [68]), interview of the children with picture cards. German version: translation by the AMIS group / Conflict Tactic Scale Parent Child (CTS-PC) ([54]), German version: target-group-specific adaptation by the authors		Child / mother	Interview through trained test administrator (Child) / Questionnaire (Mother)
	Mother’s “Minor” physical violence				
*Hypothesis 2.3*: The home visits reduce or prevent child neglect	Mother’s physical neglect	Scale of the Multidimensional Neglectful Behavior Scale-Child Report (MNBS [53]), interview of the children with picture cards. German version: translation by the AMIS group.	Primary outcome domain	Mother	Questionnaire
	Mother’s emotional neglect			Child / mother	Interview through trained test administrator (Child) / Questionnaire (Mother)
	Mother’s cognitive neglect				
	Mother’s supervisory neglect				
*Hypothesis 3.1*: The home visits have a positive effect on the mother’s perceived social support	Mother’s Perceived social support	Questionnaire regarding social support (FSOZU-K6 [71])	Secondary outcome domain	Mother	Questionnaire
*Hypothesis 3.2*: The home visits influence the mother’s mental health	Mother’s mental stress	Depression-Anxiety-Stress Scale (DASS [70]), German version: target-group-specific adaptation by the authors	Primary outcome domain	Mother	Questionnaire
*Hypothesis 3.3*: The home visits result in more stable partnerships with less frequent partner change, greater satisfaction with the partnership and less domestic violence in the partnership	Mother’s stability of partnership	Developed by the authors	Secondary outcome domain	Mother	Questionnaire
	Mother’s partnership satisfaction	Short form of the Partnership Questionnaire (PFB-K [74])			
	Psychological aggression against mother	Conflict Tactics Scales (CTS2 [54]; German version: target-group-specific adaptation by the authors [forward-backward]			
	Physical violence against mother				
	Sexual assault against mother				
	Injuries due to assaults by the partner				
*Hypothesis 3.4*: The home visits improve the parental self-efficacy expectations regarding the parenting tasks	Mother’s parenting self-efficacy	Parenting Sense of Competence Scale (PSOC) ([76]), German version: target-group-specific adaptation by the authors	Secondary outcome domain	Mother	Questionnaire
*Hypothesis 3.5*: The home visits have a positive effect on the perceived stress resulting from the mother’s parenting tasks	Mother’s parenting stress	Parenting Stress Index (PSI [72]), German version: Eltern-Belastungs-Inventar (EBI [73]).	Secondary outcome domain	Mother	Questionnaire
*Hypothesis 3.6*:The home visits have a positive effect on the mother‘s life satisfaction	Mother’s general life satisfaction	Questions regarding life satisfaction (FLZ [77])	Primary outcome domain	Mother	Questionnaire
*Hypothesis 4.1*: The home visits increase the share of mothers in employment or education programs	Mother’s acceptance of employment	The German Socio-Economic Panel (SOEP) [49] and	Secondary outcome domain	Mother	Questionnaire
	Mother’s acceptance of training or educational offers	The Panel Arbeitsmarkt und Soziale Sicherung ([78])		Mother	Questionnaire
Hypothesis 4.2: The home visits reduce the families’ use of welfare payments (SGB II, SGB III and SGB VIII [social security codes]).	Welfare payments	Integrated employment history provided by the Institute of Employment Research (IAB)	Secondary outcome domain	Institute of Employment Research (IAB)	Administrative data
Hypothesis 4.3: The home visits have a positive effect on the family’s living situation	Family situation	The Home Observation for Measurement of the Environment (HOME [59] forward-backward translation by the authors)	Secondary outcome domain	Staff	Observation
Hypothesis 4.4: The home visits influence the timing or frequency of a renewed pregnancy and births	Renewed pregnancy	Questionnaire about intended and realized fertility (Siedler et al., 2009). Integrated Employment History provided by the Institute of Employment Research (IAB)	Secondary outcome domain	Mother/ Institute of Employment Research (IAB)	Questionnaire/ administrative data
	Renewed desire to have children				
	Abortions Births				
Hypothesis 5.1: The home visits improve the mothers’ physical health	Mother’s physical health	12-Item Short Form Survey (SF-12 [79])	Secondary outcome domain	Mother	Questionnaire
Hypothesis 5.2: The home visits increase the frequency of pediatric primary care use (e.g., screenings, vaccinations, child’s oral health care and dentist visits)	Frequency of pediatric primary care use	KiGGS questionnaire [80] physician visits with ICD Z	Secondary outcome domain	Mother health insurance companies	Questionnaire/administrative data
Hypothesis 5.3: Home visits reduce the children’s hospital visits (outpatient or inpatient) caused by accidents and injuries	Number of child’s injuries	Hospital admission and physician visits with ICD S and T	Secondary outcome domain	Health insurance companies	Administrative data

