### Research question 4: The families’ socio-economic situation

#### Family income, employment and education

Different scales from the German Socio-Economic Panel (SOEP) [49] were used to asses family income, employment rates and educational status. The German SOEP study (GSOEP) is conducted by the *Deutsches Institut für Wirtschaftsforchung* (DIW – German Institute for Economic Research). It was initiated in 1984 and has been conducted annually since then.

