#### Acceptance of employment, training or educational offers

A five-item scale used in the SOEP [49] as well as in the *Panel Labor Market and Social Security* (PASS [78]) was used to measure employment attitudes. These questions contain certain statements about the importance of employment for the individual to which the participant can completely agree or completely disagree. Additionally, a six-item scale used in the SOEP and PASS assesses acceptable obstacles regarding the start of an occupation. The respondents can rate these difficulties on a 4-point Likert scale from *I will accept in any* case to *I will not accept in any case*.

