#### Welfare payments

The Research Data Centre (FDZ) of the Federal Employment Agency at the Institute of Employment Research (IAB) provides social security data (Integrated Employment History) for all participants. The participating individuals will be identified by the participants’ name, date of birth and address from the social security data. For all participants who are identified via their social security data, it is possible to merge survey and assessment data with their welfare receipt spells, amount of welfare, and additional cash transfers. Additionally, the social security data provides employment spells, wage spells and indicators about the type of occupation. The data is available from the participant’s entry into the labor market until the time of the follow-up data collection.

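### The outcomes listed for Hypothesis 4.1 are attitude scales, not the share of mothers in work or education, and the row does not clearly assign the status data that are collected

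*Protocol article*

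**What the plan says.** Under *Evaluation of effectiveness* and again in Table 1, Hypothesis 4.1 is "The home visits increase the share of mothers in employment or education programs". It is classed as a secondary outcome domain. The construct column of Table 1 lists "Mother’s acceptance of employment" and "Mother’s acceptance of training or educational offers". The operationalization entry names "The German Socio-Economic Panel (SOEP) [49] and" the PASS panel, without specifying a scale or item in either. The informant is the mother and the data source is the questionnaire.

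The text before Table 1 says that the listed procedures are described in more detail afterwards. Three descriptions under research question 4 bear on this row:

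- *Acceptance of employment, training or educational offers*: a five-item scale from SOEP and PASS "was used to measure employment attitudes"; in addition, "a six-item scale used in the SOEP and PASS assesses acceptable obstacles regarding the start of an occupation".
- *Family income, employment and education*: SOEP scales are used for "family income, employment rates and educational status".
- *Welfare payments*: "the social security data provides employment spells, wage spells and indicators about the type of occupation", available up to the follow-up for mothers who can be identified in the records.

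*Administrative data* adds that the IAB source also covers unemployment phases and participation in measures during unemployment, and that mothers could decline access to administrative data. *Data analysis* commits to family-wise error control across the different outcome measures within one hypothesis.

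**The concern.** A hypothesis about a share needs an outcome that classifies each mother as in or out of employment or education. The listed constructs, as the article itself describes them, measure how important work is to a mother and what drawbacks she would tolerate in a job. These may lie on the path to employment, but they are not employment. A programme could shift attitudes without shifting the share at work, or the reverse.

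Two things are at stake. First, an analyst who follows the row literally would let attitude scales decide a hypothesis about a proportion, while actual status would have no designated place in the test. Second, the promised multiplicity adjustment works within each hypothesis. If it is unclear whether attitudes, SOEP status, IAB spells or some mixture belong to Hypothesis 4.1, its family of tests is not fixed and could be settled after the data are seen.

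**Working it through.** The article states no figure for this point that could be reproduced, so the check sets the passages side by side.

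1. **Quantity in the hypothesis.** A share of mothers in employment or education programmes: a proportion per arm, from a yes/no status.

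2. **Quantity in the listed constructs.** The term acceptance could in ordinary use mean taking up a job or a course. Two features of the article point to attitudes instead:
   - The instrument section headed with the same label describes attitudes and willingness, not take-up.
   - The source pair matches. The Table 1 row cites SOEP together with PASS, and so does the acceptance section. The employment and education section cites SOEP alone, and PASS is described nowhere else among the instruments.

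3. **Coverage of the second construct.** Neither scale is described as dealing with training or education. The training and education construct thus has no described measure under its own label.

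4. **Where actual status sits.**
   - SOEP employment and education items are described under research question 4, but no construct in Table 1 is named employment status or educational participation.
   - IAB employment spells are described under *Welfare payments*. Table 1 assigns the IAB history to Hypotheses 4.2 and 4.4. The row for 4.1 lists only the mother and her questionnaire.

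5. **Consequence for the multiplicity family.** The article names no adjustment method, and that detail may properly sit elsewhere. Purely as an illustration, assume Bonferroni at a family-wise level of .05:
   - status alone (one test): .05 / 1 = .05
   - the two attitude scales (two tests): .05 / 2 = .025
   - both scales plus status plus IAB spells (four tests): .05 / 4 = .0125

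   All three families are compatible with some reading of the text. A different family-wise method would give different thresholds, but they would still depend on which measures are counted.

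6. **Extent.** By the Table 1 classification, primary domains are Hypotheses 1.1, 1.2, 1.4, 2.1, 2.2, 2.3, 3.2 and 3.6 (8). Secondary domains are 1.3, 1.5, 3.1, 3.3, 3.4, 3.5, 4.1 to 4.4 and 5.1 to 5.3 (13). The total is 8 + 13 = 21. The mismatch concerns one of the 13 secondary hypotheses and no primary one.

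**The case against.** The strongest reply is that the row already covers actual status. Its operationalization entry names SOEP as a whole, and the article says SOEP scales assess employment rates and educational status under the same research question. SOEP appears in Table 1 only in this row. Because the two acceptance scales do not cover training, they cannot be the full operationalization of the second construct, which suggests loose wording rather than a decision to replace status with attitudes. The article is also condensed, and item-level definitions may stand in a fuller document.

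Much of this stands. A reader might infer that the plan cannot confirm or refute Hypothesis 4.1. The documents do not support that: the status data are collected and, on one reading, come from the very instrument the row names. A reader might also infer that an attitude shift would be reported as a higher share in work. Nothing in the article says so; it is a risk of following the row literally, not a stated intention. Nor does it help to argue that mothers who know whether they were visited may shade their answers about attitudes, since employment status at interview is reported by the same mothers.

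The reply does not remove the mismatch itself. The construct labels and the source pair both lead to the attitude scales, and no text says that status is the deciding measure. This goes beyond omitted detail: the article states constructs for the hypothesis, and those constructs measure something else.

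**Conclusion.** The concern holds as a mismatch between a hypothesis and its listed outcomes. Read with the instrument section, the two constructs for Hypothesis 4.1 are attitude and willingness scales and do not measure the share of mothers in employment or education. Suitable status data are collected but not clearly assigned, so both the deciding measure and the multiplicity family are left open.

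The conclusion rests on reading acceptance in Table 1 as the article's own section of that name defines it. If the authors meant take-up of jobs and courses, the intended outcome may be right, but the label and cross-reference still need correcting. The size is modest: one secondary hypothesis, no primary outcome, and no data lost. It should be corrected because it bears on what can be claimed about the families' socio-economic situation, and because the correction is cheap.

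**What to change.** In the Hypothesis 4.1 row of Table 1:

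- name being in employment or education at interview (yes/no, from the SOEP items) as the deciding outcome;
- add IAB employment spells over a stated period as a supporting outcome, for mothers who consented and could be linked;
- label the two acceptance scales as supporting or explanatory measures outside the Hypothesis 4.1 test;
- state which of these enter the within-hypothesis adjustment promised under *Data analysis*.

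The change should be dated and made before these outcomes are compared between arms. If the registry entry, which is not available here, carries the same wording, it should be aligned.

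The cost is one table row and no new data collection. Some limits remain. Status at interview is still self-reported. The IAB data cover only consenting, linked mothers, and they may not fully capture education: the described content is employment, wages, occupation, benefits and measures during unemployment. That is why they are better placed as support than as the deciding outcome.
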